## **6.0 STUDY DESIGN AND DESCRIPTION**

### **6.1 Study Design**

Study design:

This open-label, multi-center, prospective, single-arm clinical trial is intended to evaluate the efficacy and safety of high-dose aumolertinib mesylate (hereinafter referred to as "aumolertinib") in patients with epidermal growth factor receptor-sensitive mutant (EGFR+) advanced non-small cell lung cancer (NSCLC) with brain metastases who have not received any systemic treatment. Eligible patients will be enrolled in the high-dose aumolertinib group and

receive aumolertinib 165 mg p.o., QD. The schematic overview of the study is shown in Figure 1.

[figure not shown]

**Figure 1. Schematic overview of the study**

• **Screening period (D–28 to D–1)**

Inpatients or outpatients will be screened after signing the informed consent form and undergo relevant laboratory tests and assessments. Subjects who meet all the inclusion criteria and do not meet any of the exclusion criteria may be enrolled.

• **Treatment period (C1+, D1+)**

High-dose aumolertinib group: Oral administration of 165 mg aumolertinib tablets once daily (55 mg/tablet, 3 tablets/day).

Each treatment cycle consists of 28 days of continuous administration. After treatment is started, efficacy will be evaluated once every 8 weeks as per RECIST 1.1. Patients will continue treatment until progressive disease assessed by investigator per RECIST 1.1 or until the withdrawal or discontinuation criteria are met. Patients may continue to receive the treatment even if progressive disease per RECIST 1.1 occurs as long as they still benefit from the treatment as judged by investigator (see Section 12.1.3 or 9.1.3.4 for details); if it is decided to continue the treatment, the baseline and follow-up plan will not be affected by the additional courses of treatment. Once the treatment is discontinued due to lack of clinical benefit upon judgment, it cannot be started again.

• **Follow-up period**

Subjects who discontinue the treatment due to meeting the discontinuation criteria should complete the treatment discontinuation follow-up, the 28-day safety follow-up after treatment discontinuation, and survival follow-up once every 12 weeks as specified in the study plan.

Subjects without progressive disease at treatment discontinuation will be followed up once every 8 weeks until progressive disease assessed by investigator per RECIST 1.1 (intracranial, extracranial, and systemic), even if the subject has received other anti-tumor treatments; after progressive disease, the subjects will be followed up for survival once every 12 weeks as specified in the study plan.

**6.2 Rationale for Study Design**

This study is designed as a single-arm study of high-dose aumolertinib. The rationale is as follows: 1) There are data from other TKIs at conventional/high doses as second-line/first-line treatment in patients with EGRF-sensitive mutant NSCLC with brain metastases, and aumolertinib 110 mg as second-line treatment has a good control effect on brain metastases, but the effects of higher doses need further exploration; 2) Aumolertinib as first-line treatment not only inhibits EGFR-sensitive mutations but may also suppress potentially existing T790M resistance mutations, which could delay the onset of T790M resistance mutations and provide significant clinical benefits for patients; 3) Pharmacokinetic data showed that there was a linear relationship between *in vivo* drug exposure and drug dose within the dose range of 55–220 mg, and the drug was well tolerated in subjects at the highest dose of 220 mg. Increasing the dose from 110 mg to 165 mg could potentially increase systemic and cerebrospinal fluid exposure, thereby improving the treatment efficacy for brain metastases while remaining safe and tolerable. 4) Aumolertinib exhibits high selectivity and has a weak effect on WT EGFR, resulting in low potential toxicity. As first-line treatment, it can reduce the risk of subjects being exposed to the potential toxicity of other EGFR TKIs that have relatively higher toxicity.

**6.3 Rationale for Dose Selection**

A phase I dose escalation and expansion study of aumolertinib in patients with advanced NSCLC showed that oral

administration of aumolertinib once daily within the dose range of 55–260 mg was safe and well tolerated and showed preliminary anti-tumor efficacy. Previous clinical trials showed that in second-line treatment, the mDoR of subjects in the aumolertinib 220 mg group was 15.2 months, compared to 9.0 months in the 55 mg group and 12.5 months in the 110 mg group. The results suggested that 220 mg could lead to a longer duration of response. At the same time, pharmacokinetic data showed that there was a linear relationship between *in vivo* drug exposure and drug dose within the dose range of 55–220 mg. High-dose aumolertinib may improve the efficacy for brain metastases while remaining safe and tolerable. Considering the currently available efficacy, safety, and PK data of aumolertinib in clinical studies, the high dose of aumolertinib in this single-arm study is determined at 165 mg (QD).

#### **6.4 Premature Termination or Suspension of the Study/Study Site**

##### **6.4.1 Criteria for premature termination or suspension of the study**

This study will be completed as scheduled and will not be suspended or prematurely terminated unless one or more of the following criteria for suspension or premature termination is/are met:

- 1) Information updates or other evaluations concerning the safety or efficacy of the investigational medicinal product suggest a change in the risk-to-benefit ratio, and the changed ratio is no longer acceptable to patients participating in this study.
- 2) Good Clinical Practice (GCP) is seriously violated, causing the failure to achieve the primary study objectives or imperiling patient safety.

##### **6.4.2 Criteria for premature termination or suspension of study site**

If a study site (including the investigator) is in serious breach of GCP, study protocol, or contractual agreement and is unable to ensure adequate conduct of this study, the site will be prematurely terminated or suspended.

##### **6.4.3 Procedure for premature termination or suspension of the study/study site**

If the sponsor, Institutional Review Board (IRB)/Independent Ethics Committee (IEC), or regulatory authorities choose to terminate or suspend the study/study site, the sponsor will provide a specific procedure for premature termination or suspension. Such procedure will be executed at the corresponding study site during termination or suspension of the study/study site.

## **7.0 SCREENING OF SUBJECTS**

### **7.1 Inclusion Criteria**

A subject must meet all the following inclusion criteria in order to be enrolled in this study:

1. Age  $\geq 18$  years old.
2. Histologically or cytologically confirmed NSCLC, which is confirmed by imaging as advanced NSCLC with brain metastases (including stage IV patients who are newly diagnosed or have relapsed after previous surgical treatment; according to the AJCC 8th edition lung cancer staging criteria).
3. Confirmed as EGFR-sensitive mutations in tumor tissue samples or blood samples by local laboratory (including exon 19 deletion or L858R, either existing alone or co-existing with other EGFR site mutations). If tumor tissues are available, the tumor tissue is recommended for testing; if tumor tissues are not available or the patient cannot undergo tissue biopsy, blood samples may be tested.
4. Have not received any systemic treatment after the diagnosis of NSCLC with metastases to brain parenchyma. For patients who have received local treatment, the lesion within the scope of the local treatment cannot be used as the target lesion unless the lesion has progressed.
5. Patients with at least 1 extracranial target lesion (measurable lesions that have not undergone local treatment such as irradiation or have shown definitive after local treatment, with a baseline longest diameter  $\geq 10$  mm (or  $\geq 15$  mm for lymph nodes)) and at least 1 intracranial lesion (with a baseline longest diameter  $\geq 5$  mm).
6. The brain condition is stable or that were controlled with anticonvulsants or dexamethasone at a maximum dose of 5 mg daily before the study treatment.
7. An Eastern Cooperative Oncology Group (ECOG) performance status score of 0 or 1, with no worsening over at least 2 weeks before study treatment, and a minimum expected survival of 3 months.
8. Female patients of childbearing potential are willing to take appropriate contraceptive measures and should not breastfeed from signing the informed consent to 6 months after the last dose of study treatment; male patients are willing to take barrier contraception (i.e., condoms) from signing the informed consent to 6 months after the last dose study treatment.
9. Female patients of childbearing potential must have a negative serum or urine HCG test within 7 days before enrollment in the study, and they must be non-lactating.
10. The subject voluntarily participates and signs the informed consent form in writing.

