| 

Screening period	Treatment period	Follow-up period	

Age ≥18 years old

Histologically or cytologically diagnosed with NSCLC

Metastases to brain parenchyma confirmed by imaging

Genetically confirmed as EGFR-sensitive mutations

Have not received any systemic treatment after diagnosis

ECOG PS 0–1

	

Aumolertinib, 165 mg, p.o., QD

	

Response evaluated per RECIST 1.1 once every 8 weeks until progressive disease
Primary study endpoint:
12-month PFS rate
Secondary study endpoints:
iPFS, iORR, iDCR, iDoR
ORR, DoR, DCR, OS
Safety

Patients who have discontinued treatment are followed up once every 8 weeks for progressive disease status until progressive disease, and once every 12 weeks after progressive disease for survival

	

 |                                                                 |                                                                                                                             |                                                                                                                                                                                                                                                                                                                                                                                                                                                                  | Screening period | Treatment period |  | Follow-up period | 

Age ≥18 years old

Histologically or cytologically diagnosed with NSCLC

Metastases to brain parenchyma confirmed by imaging

Genetically confirmed as EGFR-sensitive mutations

Have not received any systemic treatment after diagnosis

ECOG PS 0–1

 | 

Aumolertinib, 165 mg, p.o., QD

 |  | 

Response evaluated per RECIST 1.1 once every 8 weeks until progressive disease
Primary study endpoint:
12-month PFS rate
Secondary study endpoints:
iPFS, iORR, iDCR, iDoR
ORR, DoR, DCR, OS
Safety

Patients who have discontinued treatment are followed up once every 8 weeks for progressive disease status until progressive disease, and once every 12 weeks after progressive disease for survival

 |

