| Subject population:
Patients age≥18 years old, with histologically or cytologically confirmed NSCLC, which is confirmed by imaging as advanced NSCLC with metastases to brain parenchyma. The patients should not receive any systemic treatment in the advanced stage, and are confirmed with EGFR-sensitive mutations before enrollment (exon 19 deletion or L858R, either existing alone or co-existing with other EGFR site mutations)                                                                                                                                                                                                                                                                                                                                                                                                                                                                                                                                                                                               |                                                                 |                                                                                                                             |                                                                                                                                                                                                                                                                                                                                                                                                                                                                  |                  |                  |  |                  |                                                                                                                                                                                                                                                                                                                                                      |                                                                 |  |                                                                                                                                                                                                                                                                                                                                                                                                                                                                  |

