**Inclusion criteria:**

A subject must meet all the following inclusion criteria in order to be enrolled in this study:

1. Age  $\geq 18$  years old.
2. Histologically or cytologically confirmed NSCLC, which is confirmed by imaging as advanced NSCLC with metastases to brain parenchyma (including stage IV patients who are newly diagnosed or have relapsed after previous surgical treatment; according to the AJCC 8th edition lung cancer staging criteria).
3. Confirmed as EGFR-sensitive mutations in tumor tissue samples or blood samples by local laboratory (including exon 19 deletion or L858R, either existing alone or co-existing with other EGFR site mutations). If the tumor tissue is not available or the patient does not accept tissue biopsy, a blood sample is acceptable.
4. Have not received any systemic anti-tumor treatment after the diagnosis of advanced NSCLC with metastases to brain parenchyma. For patients who have received local treatment, the lesion within the scope of the local treatment cannot be used as the target lesion unless the lesion has progressed.
5. Patients with at least 1 extracranial target lesion (measurable lesions that have not undergone local treatment such as irradiation or have shown definitive after local treatment, with a baseline longest diameter  $\geq 10$  mm (or  $\geq 15$  mm for lymph nodes)) and at least 1 intracranial lesion (with a baseline longest diameter  $\geq 5$  mm).
6. The brain condition is stable or that were controlled with anticonvulsants or dexamethasone at a maximum dose of 5 mg daily before the study treatment.
7. The Eastern Cooperative Oncology Group (ECOG) performance status score is 0 or 1, and has not deteriorated at least 2 weeks before the study treatment, and the expected survival period is not less than 3 months.
8. Female patients of childbearing potential are willing to take appropriate contraceptive measures and should not breastfeed from signing the informed consent to 6 months after the last dose of study treatment; male patients are willing to take barrier contraception (i.e., condoms) from signing the informed consent to 6 months after the last dose study treatment.
9. Female patients of childbearing potential must have a negative serum or urine HCG test within 7 days before enrollment in the study, and they must be non-lactating.
10. The subject voluntarily participates and signs the informed consent form in writing.

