Aumolertinib can block the formation of non-selective metabolites through structural optimization, which, coupled with its high selectivity and weak effect on wild-type EGFR, result in less toxic side effects. Current clinical studies have shown that aumolertinib is well tolerated and safe, and its main adverse reactions are changes in gastrointestinal tract, skin, and laboratory tests. The first-line use of aumolertinib can reduce the likelihood and duration of patients being exposed to other TKIs that have relatively significant side effects.

In summary, the available preclinical and efficacy and safety data of aumolertinib in patients with advanced NSCLC indicate that aumolertinib as first-line treatment is expected to have good efficacy and safety in subjects with EGFR-sensitive mutant advanced NSCLC with brain metastases who have not received any systemic treatment at the advanced stage, and high doses may offer potential benefits.

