## **5.0 STUDY OBJECTIVES AND ENDPOINTS**

### **5.1 Study Objectives**

#### **5.1.1 Primary objective**

To evaluate the 12-month progression-free survival (PFS) rate of high-dose aumolertinib as first-line treatment of EGFR-sensitive mutant advanced NSCLC with brain metastases.

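### Inclusion criterion 4 bars systemic treatment only from the diagnosis of brain metastases, which does not enforce the protocol's own first-line population

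*Protocol*

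**What the plan says.** The entry rule appears twice. Section 7.1, inclusion criterion 4, reads "Have not received any systemic treatment after the diagnosis of NSCLC with metastases to brain parenchyma". The synopsis version reads "Have not received any systemic anti-tumor treatment after the diagnosis of advanced NSCLC with metastases to brain parenchyma". Both start the bar at a diagnosis that already includes brain parenchymal metastases.

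The protocol describes the population differently elsewhere:

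- Synopsis, subject population: "The patients should not receive any systemic treatment in the advanced stage".
- Section 4.3.2: patients "who have not received any systemic treatment at the advanced stage".
- Section 6.1: patients with "brain metastases who have not received any systemic treatment". The synopsis study design and the end of section 4.2.4 say the same.
- Synopsis study schema: "Have not received any systemic treatment after diagnosis", without saying which diagnosis.

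The primary objective in section 5.1.1 concerns "high-dose aumolertinib as first-line treatment of EGFR-sensitive mutant advanced NSCLC with brain metastases".

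**The concern.** Sites decide entry on the criteria in section 7, not on the narrative. If the criterion starts the clock later than the population statement does, it can admit someone whom the population statement rules out: a patient already treated systemically for advanced disease who developed brain metastases afterwards. That patient is not first-line.

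The trial has one arm and one primary estimate, the 12-month PFS rate, planned on 40% against 60% (section 5.3). There is no control arm in which a mixture of treatment lines would balance out. The full analysis set in section 12.4.1 is every patient who took at least one dose, so such a patient would remain in the main result. The estimate would then no longer answer strictly the first-line question in section 5.1.1.

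**Working it through.** No figure in the plan bears on this point, and moving the starting point of criterion 4 would not change the sample size. The check is whether any other rule does what criterion 4 leaves undone.

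Take a patient with advanced NSCLC, an EGFR-sensitive mutation and no brain metastases, who receives chemotherapy or immunotherapy. Brain metastases appear later, and the patient is screened with no systemic treatment since that finding.

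| Rule | What it covers | Does it remove this patient? |
|---|---|---|
| Inclusion 4 (7.1 and synopsis) | Systemic treatment after the diagnosis with brain metastases | No |
| Inclusion 2 | Advanced NSCLC with brain metastases, "including stage IV patients who are newly diagnosed or have relapsed after previous surgical treatment" | Unclear; see below |
| Exclusion 1a | Any previous EGFR-TKI, whatever its timing | No; the earlier treatment was not a TKI |
| Exclusion 1d | Recurrence within 6 months of adjuvant or neoadjuvant treatment for early disease | No; the treatment was for advanced disease |
| Exclusion 1e | Anti-tumor traditional Chinese medicines within 14 days | No |
| Exclusion 1i | Recent participation in another trial | Only if the earlier treatment was in a recent trial |
| Exclusion 3 | Residual toxicity above Grade 1, with exceptions | No; it limits what is left of earlier anti-tumor treatment, not the treatment itself |

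Inclusion 2 can be read in two ways.

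1. *Open list.* The word that introduces it gives examples only. The patient above then qualifies.
2. *Closed list.* Only the two named groups qualify: newly diagnosed stage IV, or relapse after surgery. The patient above then fails, unless there was earlier surgery. A patient who relapsed after surgery, was treated systemically for that relapse, and later developed brain metastases still fits the list and still meets criterion 4.

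So the closed reading narrows the gap without closing it.

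Two other provisions bear on how the gap would work in practice. Section 14.2 allows no exemptions from the criteria, and section 7.4 has the sites (about 20, per the synopsis) compete to enroll. Two sites could decide the same patient differently, each with protocol text to cite. Section 7.5, on wrongly enrolled subjects, does not help, because someone who meets the written criteria has not been wrongly enrolled.

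The two versions of criterion 4 also differ. The synopsis restricts it to anti-tumor treatment and section 7.1 does not. Taken literally, the section 7.1 wording sits awkwardly beside inclusion 6, which accepts dexamethasone for control of brain symptoms.

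**The case against.** The best defence is that the intent is plain and consistent. Every narrative description points to patients untreated in the advanced stage, and in the synopsis the phrase used in criterion 4 is close to the name of the study disease. An investigator who reads the whole protocol would probably decline the patient described above. Inclusion 3 also uses the same introductory word for its mutation list, and the synopsis population statement gives that list as a definition, which supports the closed reading of inclusion 2. Exclusion 1a removes every patient with earlier EGFR-TKI treatment, which shuts a major route. All of this stands. It makes the gap small and shows what was meant, but the operative sentence still says something else.

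Several stronger readings are tempting and not supported.

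- *A sized dilution of the primary rate.* A reader might assume that 10–20% of patients enter this way and take their 12-month rate from the CNS median PFS of 10.8 months in section 4.2.4. On an exponential curve that is 0.5^(12/10.8) = 0.463, and the expected rate falls from 60% to 0.9 × 0.60 + 0.1 × 0.463 = 58.6%, or 0.8 × 0.60 + 0.2 × 0.463 = 57.3%. The share has no source in the protocol. The median is for intracranial progression, not systemic PFS. It also comes from the second-line programme, whose patients section 4.2.4 describes as having progressed on an EGFR-TKI; exclusion 1a bars such patients here. Taking the overall phase II median of 12.3 months instead gives 0.5^(12/12.3) = 0.51, but that is the same unsuitable population.
- *A raised chance of a false-positive result.* If previously treated patients do worse, their entry lowers the observed rate and works against success over 40%. The documents give no ground for expecting the opposite.
- *A title and objectives that themselves exclude earlier treatment in the advanced stage.* They say only first-line. The explicit wording is in the synopsis population statement and section 4.3.2.

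**Conclusion.** The point holds as an internal contradiction in the current text. Criterion 4, in both places, bars less than the population statements do, and no other criterion clearly makes up the difference. It applies only to systemic treatment other than EGFR-TKIs, given for advanced disease before brain metastases were found. Probably few patients are affected. The protocol gives neither their share nor their PFS rate, so no shift in the primary estimate and no loss of power can be put on it. It is worth correcting because the primary result is a single-arm rate whose meaning depends on the patients being first-line.

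The conclusion assumes that sites apply criterion 4 as worded. It does not depend on choosing between the two readings of inclusion 2, because a gap remains under either.

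**What to change.** Reconcile criterion 4, in section 7.1 and in the synopsis, with the synopsis population statement, and use identical wording in both places. For example: *Have not received any systemic anti-tumor treatment in the advanced stage of NSCLC.* The sentence on locally treated lesions can stay, and exclusion 1d should be left unchanged so that the rule for adjuvant and neoadjuvant treatment is not disturbed.

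Do not limit the new wording to stage IV. Section 4.1 counts locally advanced disease among the advanced stages, so a stage IV limit would be narrower than the statement it is meant to enforce and would still let through systemic treatment for unresectable locally advanced disease.

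The cost is one sentence in two places. The sample size does not change, and a few patients may no longer be eligible.
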